**Method/design:**

This is a single-center, single-blinded, parallel randomized controlled trial conducted at Xi'an Honghui Hospital, a regional orthopedic medical center. Eligible patients will be recruited to participate in the study, and baseline data collection and clinical assessments will be conducted at the time of admission. Using the principle of random allocation, recruited patients will be divided into either the experimental or control group. Both groups will undergo a standard, widely promoted rehabilitation program. The patients in the experimental group will wear equipment to detect and track mobility in the lower limbs. All patients will return to the outpatient clinic for follow-up assessments at 2 weeks, 12 weeks, and 24 weeks after discharge, where outcome indicators will be measured. The primary outcome will be the cost and time after discharge, while secondary outcomes will include the 6-min walk test (6MWT), range of motion (ROM), visual analog scale (VAS), American Knee Society Score (KSS), the Western Ontario and McMaster Universities Osteoarthritis Index (WOMAC).

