### Recruitment

Xi'an Honghui Hospital is a leading orthopedic center in China. The research team will provide patients with detailed information on the purpose, content, possible risks, and benefits of the trial, in adherence with the principle of informed and voluntary consent. The study will involve patients with end-stage KOA. Following completion of pre-operative preparations, TKA will be performed. The baseline registration and clinical evaluation conducted upon admission. During hospitalization, all patients receive the same treatment regimen and are discharged within 2–4 days after surgery.

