### Randomization and blinding

The 200 recruited patients are randomly assigned in a 1:1 ratio to either the experimental or control group using a computerized random number generator. Each patient is assigned a random number. Blinding is not possible due to the nature of the study, so neither patients nor physicians will be blinded to their group assignment. However, data analysts will not have access to any patient information other than their assigned number and will remain blinded during the statistical analysis of the collected data and presentation of results.

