### Interventions

During their hospitalization, both the experimental and control groups receive the same treatment regimen, rehabilitation exercise, and nursing services. After undergoing TKA, patients in the experimental group are given wearable devices and are guided to perform rehabilitation training using an APP, while patients in the control group follow a handbook for their exercise program. The rehabilitation programs for both groups are consistent and were developed in accordance with the American Academy of Orthopaedic Surgeons (AAOS) Clinical Practice Guidelines (CGPs), the American Association of Hip and Knee Surgeons (AAHKS) guidelines, and other published literature [9, 32–34]. The rehabilitation exercise program can be found in Additional file 2. Following their discharge, both groups perform the home-based exercise program for 12 weeks. The patients in the experimental group will be required to return the devices to the research team at the 12th week. Following that, both groups of patients will no longer be required to adhere to the rehabilitation program's exercise regimen.

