### Outcome measures

At the time of hospitalization, all recruited patients complete baseline registration which includes gender, age, BMI (kg/m^2^), education level, medical insurance, dwelling place, comorbidities, and medications. Clinical assessments such as knee extension and flexion, KSS, WOMAC, and the American Society of Anesthesiologists (ASA) physical status classification are also completed. At 2 weeks, 12 weeks, and 24 weeks after discharge, 6WMT, ROM, VAS, KSS, and WOMAC of patients are evaluated. The cost and time are calculated at 12 weeks after discharge.

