### Data analysis

The study schedule is depicted in Table 1. Data of all patients are recorded in Excel format and imported into SPSS (version 26.0; Armonk, New York, USA) for statistical analysis. To minimize bias due to missing data, intention-to-treat analyses and multiple imputation methods are employed. Descriptive statistics of measurement data are presented as mean ± standard deviation, while counting data are expressed as rate and composition ratio. Continuous variables are subjected to Student's *T* test if they meet the normal distribution, and Wilcoxon rank sum test is used otherwise. Categorical variables are tested using the chi-square test or Fisher's exact test. Secondary analyses are adjusted for baseline characteristics using analysis of covariance (ANCOVA). This study involves conducting multiple hypothesis tests, which undoubtedly increases the probability of Type I errors significantly. To control for family-wise error, Bonferroni corrections are adopted, resulting in a lowered adjusted *p* value of 0.002.

**Table 1 Tab1:** The patients’ schedule of trial enrollment, interventions, and assessment

Time point	Study period					
	Inpatient			Outpatient		
	Enrollment	Allocation	Pre-operation	2w	12w	24w
Enrollment						
Eligibility screen	×					
Informed consent	×					
Allocation		×				
Rehabilitation education			×			
Interventions						
Experimental group			×			
Control group			×			
Assessments						
Basal demographics and clinical data			×			
Cost					×	
Time					×	
6MWT						
ROM						
VAS						
KSS						
WOMAC						

“×” indicates the execution of the project according to the schedule

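### Table 1 places open allocation before baseline scoring and surgery, at odds with the text; baseline should come first, the arm should be released only after surgery, and the blinding label should be corrected.

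*Protocol article*

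**What the plan says.** **Blinding.** The abstract states: "This is a single-center, single-blinded, parallel randomized controlled trial". The section Randomization and blinding says that "neither patients nor physicians will be blinded to their group assignment", and that the data analysts "will remain blinded during the statistical analysis of the collected data and presentation of results". The article does not mention blinding of outcome assessors.

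**Order of events in the text.** The abstract says "baseline data collection and clinical assessments will be conducted at the time of admission", and its next sentence describes random allocation. Recruitment says "The baseline registration and clinical evaluation conducted upon admission", and Outcome measures says "At the time of hospitalization, all recruited patients complete baseline registration"; neither relates this to allocation. Randomization and blinding gives no time point for randomisation.

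**Order of events in Table 1.** The inpatient columns run Enrollment, Allocation, Pre-operation. Allocation is marked in the second. The row "Basal demographics and clinical data" is marked in the third.

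**Start of the difference between arms.** Interventions prescribes identical inpatient care, then says: "After undergoing TKA, patients in the experimental group are given wearable devices". Table 1, however, marks both group interventions under Pre-operation.

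**The concern.** In an open trial, the order of baseline and allocation is one of the few safeguards left. The baseline includes a patient-reported scale (WOMAC), a score that an examiner completes (KSS) and measured knee flexion and extension. If these are taken after an open allocation, expectation on the part of patient or examiner can influence them. Data analysis provides for ANCOVA adjustment for baseline characteristics in the secondary analyses. A covariate measured after allocation may itself be affected by allocation, and adjusting for it can then bias the comparison instead of sharpening it.

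Allocation before surgery has two further consequences. Staff who know the arm may deliver the inpatient care that is meant to be equal and may take the discharge decision. Patients whose operation is cancelled, or who meet an exit criterion in hospital, also count as randomised although the home programme never started for them.

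The blinding label matters for the reader of the results, who will usually take single-blinded to mean that the patient or the assessor is blinded.

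**Working it through.** The plan states no figure on this point, so the check is mainly a comparison of sections.

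**1. Baseline against allocation.**
- Abstract: baseline at admission, with allocation described next.
- Recruitment and Outcome measures: baseline at admission, order relative to allocation not given.
- Randomization and blinding: no time given.
- Table 1: allocation in column 2, baseline in column 3.

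Only Table 1 fixes a sequence, and it is the reverse of the abstract's narrative. The order is therefore unsettled.

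**2. Allocation against surgery.** Only Table 1 implies that allocation precedes surgery. The abstract does not place surgery, and Recruitment describes surgery without mentioning allocation.

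**3. Allocation against the first difference in care.** By the Interventions section the arms first differ after surgery. Nothing in the article shows a need for the arm to be known earlier. Table 1's intervention marks conflict with that section.

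**4. Which analyses are touched.** Cost and time are counted over 12 weeks after discharge and have no baseline value. Baseline values enter only the adjusted secondary analyses. Baseline 6MWT and VAS are not listed among the admission assessments, so the covariates at risk are WOMAC, KSS and knee motion.

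**5. Size of the avoidable loss.** Inputs: 200 patients randomised, 80 per group needed and a loss allowance of 20-25% (Sample size). The share lost between allocation and discharge is not given; 3-5% is an assumption.
- 200 × 0.03 = 6 patients; 200 × 0.05 = 10 patients.
- At 20% total loss: 200 × 0.80 = 160, or 80 per group, exactly the stated need. The allowance is 40 patients, of which 6-10 would be 15-25% (6/40 to 10/40).
- At 25% total loss: 200 × 0.75 = 150, or 75 per group, already below the stated 80. The allowance is 50 patients, of which 6-10 would be 12-20% (6/50 to 10/50).

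Such losses fit within the allowance, but it has no slack at its lower end and falls short at its upper end.

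**6. Who is blinded.** Patients: no. Physicians: no. Outcome assessors: not stated. Data analysts: yes. One party is blinded, but not one that the label usually suggests.

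**The case against.** The strongest reply is that Table 1 is weak evidence of a timeline. It has no column for surgery, the post-operative stay or discharge, and it marks the interventions before surgery although the text starts them afterwards. Its outcome rows also carry no marks as read here, which may be an artefact of text extraction. Three sections of text agree that baseline is taken at admission. This stands to the extent that the finding is a conflict to be reconciled, not proof that baseline will follow allocation. It does not remove the point, because the schedule is what site staff are likely to work from and no other part of the article fixes the order.

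Stronger readings are tempting, but the documents do not support them:
- *Staff and patients will know the arm during baseline, surgery and the discharge decision.* The article says that patients and physicians are not blinded. It does not say when the arm is disclosed, and it does not mention ward staff.
- *Inpatient care will differ.* The plan prescribes equal care, so a difference is a risk only. The follow-up window is counted from each patient's own discharge, so the discharge day does not alter its length.
- *The single-blinded label is false.* The analysts are blinded and the section discloses who is not. The label is misleading, which is a wording matter and does not depend on when allocation occurs.
- *The primary result is biased by contaminated baselines.* Cost and time have no baseline value.

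It can also be argued that early losses under equal inpatient care should be balanced between arms, and that intention-to-treat with multiple imputation is planned. Balance is indeed the expectation, so the harm is mainly lost precision. Imputation helps less here, because a patient whose operation was cancelled has no meaningful post-operative cost to impute.

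**Conclusion.** The point holds as an unresolved conflict with a cheap remedy. Table 1 sets the less protective order in a trial where patients and physicians are open, and it disagrees with the abstract on baseline and with the Interventions section on when the arms begin to differ. Following it would leave the secondary ANCOVA covariates open to influence from knowledge of the arm, weaken the protection of equal inpatient care, and create avoidable post-randomisation losses.

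The losses come to about 6-10 of 200 if 3-5% of patients are cancelled or exit before discharge; that rate is assumed, and no document supports a particular value. The effect on the ANCOVA cannot be sized from the article. No bias in the primary outcome is shown. The change is worth making, and the Trial status section places the trial before the start of recruitment.

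**What to change.** 1. Reconcile Table 1 with the abstract, Recruitment, Interventions and Outcome measures on the order of baseline, allocation, surgery and the start of each group's intervention. Add columns for the post-operative stay and discharge so that the table can be read as a timeline.
2. State that all baseline assessments are completed and recorded before allocation.
3. State when randomisation takes place. Given that the Interventions section starts the difference between arms after surgery, release the allocation only after surgery, immediately before the device or handbook is issued. The investigators should confirm that issue point when they reconcile the sections.
4. Replace single-blinded in the abstract with open-label with blinded data analysts.

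**Cost.** A change of wording and of randomisation timing, with no extra staff. APP download and device connection must fit into what remains of the 2-4 day post-operative stay. If 200 patients are still to be randomised and 3-5% drop out before that point (the same assumption), slightly more must consent: 200/0.97 = 206.2, so 207, to 200/0.95 = 210.5, so 211. Those extra patients need a baseline assessment but no device, handbook or follow-up.

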### Interventions

During their hospitalization, both the experimental and control groups receive the same treatment regimen, rehabilitation exercise, and nursing services. After undergoing TKA, patients in the experimental group are given wearable devices and are guided to perform rehabilitation training using an APP, while patients in the control group follow a handbook for their exercise program. The rehabilitation programs for both groups are consistent and were developed in accordance with the American Academy of Orthopaedic Surgeons (AAOS) Clinical Practice Guidelines (CGPs), the American Association of Hip and Knee Surgeons (AAHKS) guidelines, and other published literature [9, 32–34]. The rehabilitation exercise program can be found in Additional file 2. Following their discharge, both groups perform the home-based exercise program for 12 weeks. The patients in the experimental group will be required to return the devices to the research team at the 12th week. Following that, both groups of patients will no longer be required to adhere to the rehabilitation program's exercise regimen.

### Control group

Patients receive guidance from physiotherapists during their hospitalization, where they learn the necessary techniques for rehabilitation exercises. After being discharged, they continue with the rehabilitation exercise program using the handbook provided to improve their quality of life.

### Experimental group and equipment components

The patients will require assistance from the doctors to download the APP and connect the devices. The devices consist of two small monitors, which are placed about 5 cm above and below the knee joint when exercising the knee joint, and about 5 cm below the knee and the dorsum of the foot when exercising the ankle joint (refer to Fig. 2). These devices can monitor the magnitude and completion of exercises and then upload the data to the physicians' workstation. Patients can watch instructional videos on the APP to learn how to wear and exercise with the devices and then start exercising actively. The APP provides prompts for exercise frequency and whether the exercise target is reached by voice. Patients can view their exercise progress on the APP, such as the completion rate and compliance rate. Additionally, they can upload their own functional and symptomatic information to the APP, such as lower limb swelling, ecchymosis, and wound healing, in the form of videos or pictures.

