**Discussion:**

We should encourage the adoption of novel, easy-to-use, supervised devices if they prove to be beneficial for patients in terms of cost, time, and effectiveness after TKA. This type of device is particularly important for people in remote rural areas, those with limited financial resources, and those who are reluctant to return to hospitals for follow-up care.

*Trial registration* Chinese Clinical Trial Registry ChiCTR2300068418. Registered on 17 February 2023.

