### Primary outcome

The primary outcome measures of this study are the cost and time spent on medical care within 12 weeks after discharge. This includes costs for transportation, consultations, mobility aids, imaging examinations, and medications, as well as the time spent during the medical visit. All costs and time are recorded in a diary. Each entry in the diary must include the date, expenses, and time spent, along with the reasons. The diary is provided to the patients in both groups by the physiotherapists before discharge for free. The unit of cost is RMB, and the unit of time is hours.

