### Secondary outcomes

Secondary outcomes consist of functional performance-based tests and rating scales. The 6MWT measures the distance a patient can walk on flat ground within 6 min. To assess ROM, the patient is required to lie flat on a bed or examination table, while the examiner measures the maximum angles of flexion and extension using a standard angle measuring instrument. VAS involves the use of a 10-cm-long line with anchor points at the ends, enabling the patient to self-assess and rate the intensity of pain. The 6MWT, ROM, and VAS can effectively reflect the knee function. In addition, the KSS and WOMAC provide a comprehensive evaluation of the patient's overall condition, including knee joint function, daily living ability, and quality of life.

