## Discussion

The knee function and quality of life of patients generally improve significantly after TKA [35]. In 1997, the concept of enhanced recovery after surgery (ERAS) was introduced and quickly expanded to orthopedic applications, particularly TKA [36]. The goal of ERAS is to shorten hospital stays without increasing the risk of postoperative complications and readmission, reduce costs, and enhance patient satisfaction with surgical outcomes [37]. Given the COVID-19 pandemic, discharging patients as soon as possible after surgery to minimize exposure in healthcare settings is recommended [38].

Interest in telemedicine as a means of providing rehabilitation guidance after TKA is growing rapidly, fueled by the explosive growth of the Internet [22]. Digital health technology is an emerging telemedicine service that can remotely supervise patients for rehabilitation exercise [31, 39]. By using video or image interaction modes, patients can increase their interest and motivation for rehabilitation exercise [40]. Although supervised rehabilitation exercise has no additional functional benefits, telemedicine services are recommended to supervise patients in performing home-based rehabilitation exercise and improve their compliance [31, 40–42]. This study provides novel, simple, and supervised wearable devices that improve patients' sense of participation and provide timely feedback on their condition. This device will provide clinicians with a comprehensive understanding of the patient's physical health, enabling them to tailor treatment plans according to the patient's needs. Additionally, it can help overcome geographical and transportation barriers, particularly in remote rural and urban areas.

In conclusion, we anticipate that this device will bring benefits to patients. If successful, it has the potential to enhance medical services and warrant promotion, especially considering China's large and aging population.

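### No complication outcome is planned, and only the device arm can upload wound and symptom information between visits, so a by-arm count of reported harms would not compare like with like

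*Protocol article*

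**What the plan says.** All places are in the protocol article.

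- **Primary outcome:** "The primary outcome measures of this study are the cost and time spent on medical care within 12 weeks after discharge". Both are recorded in a patient diary issued to both groups, with a reason for each entry.
- **Secondary outcomes:** "Secondary outcomes consist of functional performance-based tests and rating scales". The abstract and Outcome measures list the same five: 6MWT, ROM, VAS, KSS and WOMAC.
- **Exit criteria; Ethics and dissemination:** infection, fracture, pulmonary embolism and wound dehiscence are examples of events that lead to exit. Exit reasons and adverse events go to the ethics committee. No comparison of them between arms is stated.
- **Experimental group and equipment components:** patients may send videos or pictures through the app: "they can upload their own functional and symptomatic information to the APP, such as lower limb swelling, ecchymosis, and wound healing".
- **Control group:** after discharge "they continue with the rehabilitation exercise program using the handbook provided". No upload or equivalent channel is described.
- **Abstract, Method/design:** "All patients will return to the outpatient clinic for follow-up assessments at 2 weeks, 12 weeks, and 24 weeks after discharge".
- **Randomization and blinding:** patients and physicians know the allocation; only the data analysts are blinded.
- **Abstract, Discussion:** adoption is to be encouraged for such devices "if they prove to be beneficial for patients in terms of cost, time, and effectiveness after TKA".

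**The concern.** Both primary outcomes measure use of care. A visit that does not take place lowers cost and time whether it was unnecessary or needed. A reader who sees a saving will want to know whether complications were at least similar in the two arms, and the stated outcomes do not supply that.

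The only complication data described are the events recorded as exits or reported to the ethics committee. If these were tallied by arm, the tally would come from an open-label trial in which one arm has an additional way to show a swollen leg or a slow wound between visits. A difference, or the lack of one, could then come from how events were found. The article also looks toward patients who are reluctant to come back to hospital, for whom this question matters most.

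**Working it through.** The article gives no complication rate, detection rate or safety sample size, so there is no stated figure to reproduce. The check has three parts.

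**1. Routes by which an event can come to light**

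| Route | Device arm | Control arm |
|---|---|---|
| Clinic visits at 2, 12 and 24 weeks | yes | yes |
| Cost and time diary with reasons, to 12 weeks | yes | yes |
| Exit and adverse-event reports to the ethics committee | yes | yes |
| Optional image or video upload of symptoms and wound | yes | none described |

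Three routes are common to both arms and one is not. The difference therefore lies between visits: before week 2, and in the 12 − 2 = 10 weeks between the second-week and twelfth-week visits. The devices are returned at week 12.

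**2. What unequal detection could do (illustration; all rates assumed)**

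Observed rate = true rate × probability of detection. With equal true risk, the observed ratio is the ratio of the detection probabilities.

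- True rate 5% in both arms, detection 90% (device) and 60% (control): 0.05 × 0.90 = 4.5% against 0.05 × 0.60 = 3.0%, ratio 1.5.
- Control detection 80%: 0.90 / 0.80 = 1.13. Control detection 50%: 0.90 / 0.50 = 1.8.
- Detection 95% against 70% or 50%: 1.36 or 1.90.

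These ratios only restate the assumed detection rates. They show the mechanism and its direction for minor events, and do not estimate its size in this trial.

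**3. How precise a fair comparison would be**

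The Sample size section recruits 200, that is 100 per arm. With 20% loss, 100 × 0.80 = 80 analysed per arm, which agrees with the stated 80.

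- Half-width of the 95% interval for a difference, assumed 5% in each arm: 1.96 × √(2 × 0.05 × 0.95 / 80) = 1.96 × 0.0345 = 0.068, about ±6.8 percentage points. With all 100 per arm: 1.96 × 0.0308 = 0.060, ±6.0 points.
- No events among 80: exact upper limit of the two-sided 95% interval = 1 − 0.025^(1/80) = 4.5%. Among 100: 1 − 0.025^(1/100) = 3.6%.
- Power to detect a doubling with 80 per arm (normal approximation, two-sided 0.05), for assumed control rates of 1%, 2%, 5% and 10%: 8%, 11%, 22% and 42%.

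A safety comparison in this trial can therefore bound a difference only loosely.

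**The case against.** The strongest reply is that this is a condensed article. How adverse events are elicited and tabulated may well be set out in the full protocol or analysis plan, and the article already sends events from either arm to the ethics committee. That stands for the details of adverse-event recording, and safety oversight does exist. It does not answer the point about outcomes, because the article states its primary and secondary outcomes as a complete list and complications are not in it. The lack of a row in Table 1 adds little to this; the outcome sections carry the point.

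Other parts of the reply also stand:

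- Uploading is optional and is not described as a source of adverse-event data. A reader might infer that physicians review the images, but the article mentions the physicians' workstation only for exercise data.
- Scheduled visits are identical, and the events named under Exit criteria are serious enough that most would probably surface without a photograph. The asymmetry mainly concerns minor events between visits.
- A reader might infer that the device would be recommended on cost and time alone. The abstract also names effectiveness, although effectiveness here is measured by function, pain and knee scores and not by complications.
- A reader might take the Discussion's phrase "shorten hospital stays without increasing the risk of postoperative complications and readmission" as the trial's own benchmark. It describes the general goal of enhanced recovery programmes, and this trial does not vary hospital stay.
- The diary records why care was sought, so it would be too strong to say that the trial learns nothing about whether visits were needed. It cannot show care that was forgone.

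**Conclusion.** The point holds in a limited form. The stated outcomes include no complications, readmission or reoperation, and one arm of an unblinded trial has an extra route by which symptoms and wound problems can come to notice. A by-arm tally of reported events could therefore mix detection with risk, and a saving in cost or time could not be read beside a fair count of harms.

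The net direction is not known. More complete detection of minor events would count against the device, while problems missed because a patient stayed away would flatter whichever arm they occurred in. The documents give no basis for a size; the ratios of 1.13 to 1.90 above rest wholly on assumed detection rates.

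A reader might go further and ask that any recommendation depend on the safety result. The numbers do not support that: with about ±6.8 points at an assumed 5% rate, low power and no stated margin, the comparison can only be descriptive. This is a cheap improvement to the design and does not undermine the cost and time comparison itself.

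**What to change.** - Add to Secondary outcomes and to Table 1 a descriptive safety outcome: the events named under Exit criteria, plus readmission and reoperation.
- Collect it in both arms with the same short checklist at the existing 2-, 12- and 24-week visits. Complete the checklist, subject to consent, also for patients who meet an exit criterion; otherwise it misses those it is meant to count.
- Base the by-arm comparison on events found at those visits or confirmed by treatment or admission records. List events known only from app uploads separately.
- Report counts per arm and the difference with a 95% confidence interval beside cost and time, labelled descriptive and without a pass or fail rule.

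The cost is a few minutes per visit, one table row and one results table. The interval will be wide. The article states that recruitment has not begun, so on its own account the change can be made before any data accrue.
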